### Protocol proposal

#### Trial design.

This randomized placebo-controlled trial will consist of 2 groups: (1) DHA+EPA and (2) Placebo (Fig 2). Written informed consent will be obtained from all participants by the study coordinators. If individuals meet inclusion/exclusion criteria, pre-supplement baseline data will be gathered, including demographics, blood spot sample for assessment of omega-3 FA composition, dietary recalls for estimation of antioxidant intake, and symptom checklist. Participants will ingest DHA+EPA or placebo supplements daily throughout the 8-week supplementation phase and the subconcussion intervention phase. Participants in both groups will be required to ingest the supplement while monitored virtually, via Zoom or Facetime. Female participants’ menstrual cycle (MC), as determined by self-report, which will be further validated by salivary progesterone levels, will be monitored during the supplementation phase to determine regular or irregular MC and MC phases. During the biweekly visit, a blood spot sample will be collected to measure DHA+EPA levels and other FAs in the blood. During the subconcussion intervention phase, participants will be fitted with a wrist-worn Actigraph to monitor their activity/sleep levels. The subconcussion intervention will involve performing 20 controlled soccer headings per session. Participants will undergo 2 sessions in a 2-day period. Blood sample, MR data, autonomic reactivity, and clinical measures (symptoms, oculomotor, cognition) will be collected at pre-heading and 24-hour post-1^st^ session, 24-hour post-2^nd^ session, and 7-day post-2^nd^ session. Fig 1 indicates the current status of enrollment and Fig 2 depicts the study flow.

**Fig 1 pone.0321808.g001:**
[figure not shown]
SPIRIT Checklist. SPIRIT schedule of enrollment includes participants who have been enrolled in the trial. Given the early stage of the study, no participants have advanced to outcome data collection as of March 2025.

**Fig 2 pone.0321808.g002:**
[figure not shown]
Schematic study design. Study figure depicts the flow of the study.

### Randomization and blinding

Using the *R* randomization function, randomly stratified IDs that correspond to study groups will be generated. Randomly stratified sequentially numbered IDs will be placed in sealed envelopes by a blinded statistician, and containers of identical appearance will be prepared by a study coordinator, who will oversee the allocation of correct supplementation. Participants will be blinded to their group assignment. For participants with a vegetarian diet, they will be nonrandomly assigned equally to each group.

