**Exclusion Criteria**
Are currently pregnant Have had a head or neck injury within the past 6 months Have implanted metal/magnetic devices (e.g., orthodontic braces) Diagnosed with autonomic or cardiovascular disease (e.g., hypertension) Allergy to fish or shellfish Consuming omega-3 FA supplements including plant-based (e.g., flaxseed) in the past 3 months Consume oily fish (>2 servings/month: salmon, bluefin, swordfish, anchovies)

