### Sample size

Based on the sample calculation for each aim, we will recruit a minimum number of subjects needed to conduct all aims. Thus, 208 participants (n=104 per primary group) will be recruited. *Alpha level setting:* The primary groups (DHA+EPA vs. placebo) share 3 post-heading time points (1^st^ 24h, 2^nd^ 24h, 168h), which will be compared to the pre-heading baseline. Thus, we set the alpha level at 0.017 to account for multiple comparisons. Based on the estimated effect sizes and alpha level, a sample size of 90 (Aim 1), 74 (Aim 2), and 82 (Aim 3) per primary group will result in 90% power to detect the supplementation effect. We accounted for a dropout rate of 15%, resulting in n=104 per group needed to accomplish all aims.

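### Vegetarian participants are assigned to arms nonrandomly in a trial labelled randomized; a blocked vegetarian stratum would give the same balance and keep the randomisation.

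*Protocol article*

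**What the plan says.** The section Randomization and blinding first describes a random scheme: "Using the *R* randomization function, randomly stratified IDs that correspond to study groups will be generated". The numbered IDs go into sealed envelopes, filled by a blinded statistician. The strata are not named. On supply it says that "containers of identical appearance will be prepared by a study coordinator, who will oversee the allocation of correct supplementation", and on blinding that "Participants will be blinded to their group assignment". It ends with the exception: "For participants with a vegetarian diet, they will be nonrandomly assigned equally to each group".

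Four other places bear on the point:

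- Trial design gives the label: "This randomized placebo-controlled trial will consist of 2 groups: (1) DHA+EPA and (2) Placebo (Fig 2". It also says who takes consent: "Written informed consent will be obtained from all participants by the study coordinators".
- Table 2 has diet-related exclusions, among them "Consume oily fish (>2 servings/month: salmon, bluefin, swordfish, anchovies" and recent omega-3 supplements, but none for a vegetarian diet.
- Sample size counts everyone together: "Thus, 208 participants (n=104 per primary group) will be recruited".
- Data analysis compares the two groups through the group by time interaction. It does not mention vegetarians.

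**The concern.** Wanting vegetarians spread evenly over the arms is reasonable. Baseline omega-3 status is a listed covariate, and a subgroup factor within the DHA+EPA arm. The difficulty is the method chosen to get that balance.

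Equal numbers make the arms alike in the proportion of vegetarians and in nothing else. Sex, concussion history, heading exposure and unmeasured factors are balanced among the vegetarians, in expectation, only if chance decides who goes where. Without a stated random sequence, whoever assigns a vegetarian may choose the arm or be able to foresee it. The article does not say who that is. Study coordinators take consent, and a study coordinator oversees allocation of the supplements, so enrolment and allocation are not clearly separated.

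At stake is the basis for comparing the arms in this subset, and the accuracy of the description of the trial as randomized. A later analysis plan cannot restore this: once a participant has been assigned nonrandomly, modelling can adjust for measured factors only.

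**Working it through.** **1. Is the sentence limited or corrected elsewhere?**

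| Question | What the article shows |
|---|---|
| Are vegetarians eligible? | Yes; Table 2 does not exclude them |
| Are they outside the 208? | No; Sample size makes no exception |
| Are they analysed apart? | No; Data analysis does not mention them |
| Is a random rule given for them? | No; the only stated rule is nonrandom and equal |
| Is random balance available in the same scheme? | Yes; stratified random IDs in sealed envelopes |

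The sentence therefore stands as written.

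**2. The plan's own figures.** The section Sample size gives alpha 0.017, 90% power, 90 evaluable per group for Aim 1 and 104 recruited per group.

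- Alpha: 0.05 / 3 = 0.0167, rounded to 0.017.
- Recruitment: 90 × 1.15 = 103.5, rounded up to 104, which reproduces the stated number.
- The effect size is not stated. Back-solved for a two-sided test (sidedness is also not stated): d = √(2/90) × (2.387 + 1.282) = 0.1491 × 3.668 = 0.547 SD.

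**3. How large could the bias be?** The article gives neither the vegetarian share nor any between-arm difference among vegetarians, so both are assumptions. Let v be the share of vegetarians and g the between-arm difference among them that arises from nonrandom assignment. The primary contrast is change from pre-heading to 24 hours after heading, so g must be a difference in that change, in SD units. With equal numbers of vegetarians per arm:

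bias = v × g

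With n = 104 × 0.85 = 88.4, taken as 88 per arm, and no true effect:

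type I error = P(Z > 2.387 − s) + P(Z < −2.387 − s), where s = bias / √(2/88) = bias / 0.1508

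Worked case, v = 15% and g = 0.5: bias = 0.075; s = 0.075 / 0.1508 = 0.497; type I error = 0.0294 + 0.0020 = 0.0314.

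| Share v (of 208) | g (SD of change) | Bias (SD) | Share of 0.547 SD | Type I error |
|---|---|---|---|---|
| 5% (10) | 0.2 | 0.010 | 1.8% | 0.0172 |
| 5% (10) | 0.5 | 0.025 | 4.6% | 0.0185 |
| 10% (21) | 0.2 | 0.020 | 3.7% | 0.0180 |
| 10% (21) | 0.5 | 0.050 | 9.1% | 0.0232 |
| 15% (31) | 0.2 | 0.030 | 5.5% | 0.0192 |
| 15% (31) | 0.5 | 0.075 | 13.7% | 0.0314 |

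Using 90 per arm instead of 88, the two outer 0.5 SD rows become 0.0186 and 0.0317. An extreme g of 1 SD at 15% gives 0.0824, but step 3 offers no basis for a difference that large.

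**The case against.** **The wording may be loose.** The authors may have meant forced balance or a separate vegetarian stratum. That is possible, and it leaves some doubt about what will be done. But the sentence follows closely on two mentions of random stratified IDs, so it reads as a contrast. If it is loose, it misstates the allocation method and still needs replacing.

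**Concealment may be intact.** A reader might infer that allocation is unconcealed for vegetarians, or that the second of each pair is always known. The article supports neither. It mentions no pairs and no rule, does not place vegetarians outside the envelopes and identical containers, and makes no exception to participant blinding. A condensed article may also leave such mechanics to the full protocol. This objection stands: predictability is a risk, not an established fact.

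**The primary contrast is a change from baseline.** Stable differences in level between the vegetarians in each arm cancel. To bias the test, assignment would have to be related to later response to heading or to the supplement, which is hard to foresee at enrolment. The plan also evaluates baseline covariates, including omega-3 composition. This stands too. It makes 0.5 SD closer to a pessimistic value than a central one, and the 1 SD case should carry no weight. It does not make the assignment random.

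**The affected group is probably small.** A reader might conclude that the p-values or the randomized label fail for the whole trial. That goes too far: all other participants are randomised, and at a 0.2 SD difference the test stays between 0.017 and 0.019.

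**Conclusion.** The point holds in a limited form. The article fixes nonrandom allocation for an eligible subset of a trial it calls randomized, nothing in it corrects this, and the same scheme could give the wanted balance with random allocation. That conclusion rests on the text alone.

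The numerical consequence is unknown. The illustration runs from practically no effect to a true error rate of about 0.031 against 0.017. It depends on an assumed share of 5% to 15%, an assumed difference of up to 0.5 SD in pre-to-post change, a two-sided test and 88 evaluable per arm. A share below 5% would make the effect smaller still.

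The reason to act is that the flaw cannot be repaired after assignment and is cheap to remove now. Recruitment runs from February 2025 to March 2028, and the caption of Fig 1 reports that nobody had reached outcome collection as of March 2025.

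**What to change.** Replace the exception in Randomization and blinding. State that vegetarian diet (yes/no) is a stratification factor in the R list, that the vegetarian stratum has its own permuted blocks, and that these participants are allocated 1:1 through the same sealed envelopes as everyone else. Balance is then kept to within one incomplete block.

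Record every vegetarian assigned nonrandomly before the change, and report a sensitivity analysis without them. Removing them from the primary analysis is a further step that is open to debate, because it costs some sample; the sensitivity analysis shows whether they matter.

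The cost is a line in the randomisation code, a short amendment and one small extra analysis. The sample size stays at 208, with no added visits. The sensitivity analysis will be slightly less precise, by however many such participants there are.

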### Study interventions

#### DHA+EPA intervention.

Participants will receive a batch of supplements to last 2 weeks during bi-weekly visits and be instructed to ingest supplements during 1-min Zoom or FaceTime call with the research coordinator each day. For the DHA+EPA intervention, each soft gel capsule contains 480 mg of DHA, 205 mg of EPA, 145 mg of other omega-3 FAs, and 10 mg of vitamin E. Participants in the DHA+EPA group will ingest 5 capsules daily [a total of 3.4 g/d: DHA (2.4 g), EPA (1.0 g)]. Individual percentage changes in DHA+EPA composition at 8 weeks may be considered as a covariate in analyses if we observe heterogeneous changes in DHA+EPA levels. Organic soybean oil softgel capsules will be used as a placebo condition for the DHA+EPA capsules. One capsule contains 485 mg of organic soybean oil, including negligible amounts of DHA (1.1 mg), EPA (1.7 mg), and vitamin E (10 mg). Participants will ingest 5 capsules daily. The placebo capsule’s shelf life, composition, shape, and size are the same as the DHA+EPA capsules.

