#### Blood fatty acid composition.

At baseline and after 8 weeks of supplementation, a fasting capillary blood sample from a fingertip will be collected and sent to OmegaQuant Analytics for blood FA composition analysis [32].

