### Subconcussion intervention

A standardized and reliable soccer heading protocol will be used for the experiment. The ACT Head Impact Tracker head sensor Pro, embedded in a head-band pocket and positioned directly below the external occipital protuberance (inion) will be used to monitor linear and angular head accelerations. A JUGS soccer machine will be used to simulate a soccer throw-in with a standardized ball speed of 30 mph. Subjects will stand approximately 40 ft away from the machine to perform the heading [33]. Participants perform 20 headers with 1 header per 30 seconds. Both groups will undergo additional heading sessions 24 hours after the first session. The participants will be instructed to direct the ball in the air back toward the research staff standing 20ft in front of the participant. If the participant fails to return the ball in the air and/or within 60° in front, which will result in a low head acceleration, they will re-do the header.

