### Data analysis

#### Primary analysis.

A multivariable mixed-effect regression model (MMRM) will be used to analyze each aim separately to examine the protective effects of DHA+EPA against subconcussive neural injury. As mentioned, the primary time point is set to 24h post-heading. The models will account for repeated measures from the same participants. We expect changes in neurological outcomes (structural, physiological, autonomic impairments, cognition/N-O function) over time to differ between groups, which is reflected in the group (DHA+EPA vs. Placebo) by time (pre- vs. post-heading) interaction. Although we primarily treat time as a categorical variable (pre, 1^st^ 24h, 2^nd^ 24h, 7d, post), we will rerun the model by treating time as a continuous variable (post-heading length) as part of sensitivity analysis. All possible baseline covariates, such as demographics, omega-3 FA compositions, heading kinematics, psychiatric factors, and antioxidant levels, will be evaluated in the context of group difference.

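### The protocol leaves room to adjust treatment comparisons for the 8-week change in blood DHA+EPA, a post-randomisation mediator, and it calls heading kinematics a baseline covariate

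*Protocol article*

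**What the plan says.** Protocol article, DHA+EPA intervention: "Individual percentage changes in DHA+EPA composition at 8 weeks may be considered as a covariate in analyses". The condition attached is that the observed changes turn out to be heterogeneous. The section on blood fatty acid composition fixes the timing: "At baseline and after 8 weeks of supplementation, a fasting capillary blood sample from a fingertip will be collected". The covariate is therefore known only after 8 weeks of assigned treatment.

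The primary analysis tests the group-by-time interaction in a repeated-measures mixed model, with pre-heading as one of the time levels and 24 hours post-heading as the primary time point. The secondary analysis compares the two groups at post-heading time points, chiefly 24 hours after the second session and 168 hours.

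On covariates, the primary analysis section puts its whole list under the label of baseline. The list opens with demographics and omega-3 composition and then ends: "heading kinematics, psychiatric factors, and antioxidant levels, will be evaluated in the context of group difference". Under Subconcussion intervention, the kinematics come from a head sensor worn while heading, which "will be used to monitor linear and angular head accelerations".

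**The concern.** The 8-week rise in blood DHA+EPA is what the supplement is meant to produce. The Discussion postulates that DHA acts by protecting neural cell membranes. A treatment comparison that holds the rise equal between arms asks what the capsules do apart from raising DHA+EPA, which is not the trial's question.

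The covariate is also strongly tied to arm, so it inflates the standard error even when it carries none of the effect. Because the condition for using it is undefined and is judged on post-randomisation data, the adjustment could enter a confirmatory comparison after the data have been seen.

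Heading kinematics are a lesser instance of the same problem: a variable recorded after randomisation and 8 weeks of supplementation is listed as baseline. The article also uses the word baseline both for the pre-supplement visit and for the pre-heading visit, so the label alone does not tell the analyst which omega-3 measurement is meant.

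**Working it through.** **Contrast between arms (DHA+EPA intervention section).** Active: 5 × (480 + 205) mg = 3,425 mg/d. Placebo: 5 × (1.1 + 1.7) mg = 14 mg/d. Taken over all participants, changes in DHA+EPA will differ widely unless supplementation fails.

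**The plan's own figures (Sample size section).** Alpha is 0.05/3 = 0.0167, stated as 0.017. Aim 1 has 90 per group at 90% power, and 90 × 1.15 = 103.5, rounded up to the stated 104. No effect size is printed. Assuming a two-sided test of two means, the implied standardised difference is d = (2.387 + 1.282) × √(2/90) = 0.547. With 104 × 0.85 ≈ 88 completers per arm and d = 0.55, unadjusted power is Φ(0.55/√(2/88) − 2.387) = Φ(1.26) = 0.90.

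**Assumptions.** The article gives no expected rise in DHA+EPA. I take 0% (SD 15) on placebo and the three active-arm cases below. The mediated share is set to 0, half or all of the effect.

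**Form A: change-score model, or covariate-by-time term.** The share of covariate variance explained by arm is R² = (mean difference²/4) / (mean difference²/4 + average within-arm variance). The standard error is multiplied by 1/√(1 − R²). For a rise of 100% (SD 40), R² = 2500/(2500 + 912.5) = 0.73 and the factor is 1.93. Simulated power (1,500 trials per case; unadjusted 0.88-0.90 in the first case):

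| Active-arm rise (SD), % | R² | SE factor | No mediation | Half | Full |
|---|---|---|---|---|---|
| 100 (40) | 0.73 | 1.93 | 0.32 | 0.08 | 0.015 |
| 100 (60) | 0.57 | 1.52 | 0.50 | 0.11 | 0.02 |
| 50 (30) | 0.53 | 1.45 | 0.57 | 0.13 | 0.015 |

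The normal formula agrees. With no mediation in the first case, 3.65/1.93 = 1.89 and Φ(1.89 − 2.387) = 0.31. The estimate itself goes from about 0.55 SD to about half under half mediation and to about 0 under full mediation. With no mediation it is unbiased.

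**Form B: main effect only in the mixed model.** The covariate has one value per participant, so it moves all of that participant's time points equally. In simulated complete data (four time points, unstructured covariance, 90 per arm, rise 100%, SD 40), the group-by-time estimate with and without it agreed to about 1e-14.

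The group difference at a single post-heading time point does change. Take equal correlation between visits, and an effect that appears only after heading, at 3 of 4 time points. The expected adjusted difference is then d × (1 − mediated share × 3/4):
- Full mediation: 0.547 × 0.25 = 0.14 SD. A spurious pre-heading difference of −0.75 × 0.547 = −0.41 SD appears.
- Half mediation: 0.547 × 0.625 = 0.34 SD.
- No mediation: unbiased, but the standard error is multiplied by √(1 + (VIF − 1)(1 + 3ρ)/4), where VIF = 1/(1 − R²). With VIF = 3.74 and an assumed between-visit correlation ρ = 0.5, this is √(1 + 2.74 × 0.625) = 1.65. Power falls from 0.90 to Φ(3.67/1.65 − 2.387) = 0.44. With VIF = 2.11 the factor is 1.30 and power is 0.67.

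A simulation of 1,000 trials per mediated share (rise 100%, SD 40) gave 0.138 and −0.414 SD under full mediation, 0.345 SD under half mediation, and power 0.455 with no mediation.

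**Heading kinematics.** The trial design puts the heading sessions after the 8-week supplementation phase. A sensor reading taken during heading cannot be a baseline value.

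**The case against.** The text says the covariate may be considered, without tying it to the primary analysis, and the primary analysis section names only baseline covariates. That stands: a reader might infer that the protocol requires this adjustment, and it does not.

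The sentence follows the active dose, so heterogeneous may refer to varying response within the supplemented arm. That reading is fair, and it makes the trigger less automatic. It does not remove the problem. Once triggered, nothing confines the covariate to that arm, and with a wide active-arm SD of 60 points R² is still 0.57.

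The strongest objection is that a person-level main effect cannot alter the group-by-time contrast in complete data. This is correct. A reader might infer that any adjustment takes power from about 90% to about 2%. That needs both full mediation and a covariate-by-time term or change-score model, and the article specifies neither. The objection does not protect the secondary comparisons at post-heading time points.

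A reader might also infer that evaluating covariates by group difference could itself remove the treatment effect. The documents do not support this: they state no test, threshold or entry rule. Even if ten true baseline covariates were selected on imbalance (|t| > 1.96), simulation left the estimate at 0.545-0.546 against 0.547, power at 0.89-0.90, and type I error at 0.011-0.017 against 0.017.

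Finally, the covariate list is commonly left to a statistical analysis plan. That is so, and the absence of a fixed list is not the point here. The point is a rule that the article does state, and a variable that it labels wrongly.

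**Conclusion.** The point holds as a permission that should be withdrawn. The protocol allows a post-randomisation mediator into unspecified analyses on an undefined trigger.

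With a time interaction or a change-score model, the primary effect would shrink in proportion to the mediated share, and power would be roughly 30-57% even with no mediation. As a main effect only, the primary contrast is safe in complete data. The post-heading group difference could still fall from about 0.55 to 0.14 SD under full mediation, or its power from 0.90 to about 0.44-0.67 with none.

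These sizes are illustrative. They rest on assumed rises in DHA+EPA, assumed mediated shares, a between-visit correlation of 0.5 for the main-effect case, and an effect size back-solved from the stated sample size. The direction does not depend on the exact values. Listing heading kinematics as baseline is a plain mislabel of lesser consequence.

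**What to change.** In the DHA+EPA intervention section, state that the 8-week change in DHA+EPA will not be a covariate in any randomised treatment comparison, primary or secondary, and will be used only in a dose-response or mediation analysis labelled exploratory. In the primary analysis section, limit the primary model's covariates to variables measured before supplementation, say that omega-3 composition means the pre-supplement value, and move heading kinematics to a sensitivity analysis labelled as post-randomisation.

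The cost is a wording amendment. The sample size and data collection do not change, and the dose-response question is kept. The article reports that no participant had reached outcome collection as of March 2025, so the change is best made before outcome data can influence it.
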